### Secondary outcomes

The secondary outcomes will be measured at 8 and 52 weeks, and differences between lithium and quetiapine assessed at both time points. Continuous secondary outcomes measured over time will use appropriate generalised linear models, covarying by baseline score where applicable. Where there are repeated measures of a continuous variable, the analysis will be set in the mixed model framework. Time to event variables will be analysed using survival methods. The secondary outcomes are as follows:Clinician-rated depression severity (continuous total score on the MÅDRS).Clinician-rated response and remission rates (defined as proportion with ≥50% reduction in baseline MÅDRS total score and MÅDRS total score ≤ 10, respectively).Global improvement (proportion of patients with a CGI-improvement score of ‘much’ or ‘very much improved’).Health-related quality of life (summary index EuroQol-5D, EQ-5D score [38]).Social functioning (continuous total Work & Social Adjustment Scale (WSAS) score [39]).Self-report adherence to treatment (5-item Medication Adherence Report (MARS-5) continuous total scores and exploratory cut-offs categorising patients as either adherent or non-adherent [40]).Physical health parameters: weight (kg) and blood pressure (mmHg).Time to commencement of trial medication from randomisation (and number of patients commencing therapy in each arm).Time to uptake of a new intervention for depression from randomisation (pharmacological or non-pharmacological) over 12 months (and proportion of patients in each arm receiving new interventions).Side Effects (continuous total score on the Patient Rated Inventory of Side Effects (PRISE) [41]).Frequency of Serious Adverse Events (SAEs).

Secondary outcomes, except for SAEs, will be adjusted for multiple comparisons. SAEs will be tabulated as number of SAEs in each group, and number of people reporting an SAE in each group over 12 months. We will also summarise the reasons for clinicians not prescribing and patients not commencing the medication they are randomised to, reasons for treatment discontinuation, the number of withdrawals, and the reasons for withdrawals from the trial. However, we will not test the difference between the groups on these variables statistically.

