### Statistical methods for analysing primary and secondary outcomes

A full statistical analysis plan will be drawn up prior to completion of data collection. The main analysis will follow an intention to treat (ITT) principle, whereby patient data are analysed by treatment group, regardless of the medication status of patients throughout the follow-up period.

Participant flow will be presented in a CONSORT diagram. For analysis of the listed primary and secondary outcomes, missing baseline data will be filled in using imputation [47]. Models will covary for randomisation stratification factors throughout. For the self-report QIDS-SR score a linear mixed model, covarying by baseline score, will be used for the estimation of the mean treatment difference and 95% confidence interval (CI) over the course of the trial. Full information maximum likelihood methods will be used for analysis, which will account for missing data under the missing at random assumption. Error distributions will be checked using Q-Q plots. Time to discontinuation will be calculated from first prescription date to treatment discontinuation, and will be analysed using Kaplan-Meier methods and Cox regression models, providing the hazard ratio for treatment discontinuation in lithium versus quetiapine, and associated 95% CI.

Continuous secondary outcomes measured over time will use generalised linear models appropriate to the variable distribution covarying by baseline where applicable, and using mixed models where there are repeated measurements. Adjustment for multiple testing will be presented [48].

For measures where missingness is above 5% and where the absence of repeated measurement gives less confidence in the adequacy of the missing data properties of maximum likelihood, we may undertake a sensitivity analysis within a multiple imputation framework [49].

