### Power calculation

Based on our power calculation and superiority design, we require 276 patients to be randomised. When considering the sample size required, we have considered both the primary outcome measures of time to all cause treatment discontinuation and longitudinal symptom severity as assessed by QIDS-SR scores. This sample size was calculated based on the following assumptions:
*Treatment discontinuation:* estimated 20% discontinuation from treatments by 8 week follow up visit (as per Bauer et al., 2013) [20]), and 50% treatment discontinuation for lithium and 30% for quetiapine by 52 weeks.
*Missing data:* 40% missingness for each of the post-randomisation QIDS-SR scores was allowed for. While the missingness has been assumed independent over time, the QIDS-SR scores are assumed uniformly correlated with a correlation of 0.6 [47]. We have allowed the discontinuation status at follow-up to be unknown for 10% of the sample.
*Effect size:* The minimum clinically significant difference for outcomes in depression treatment is widely taken to be 3 points on the HDRS [3, 50]. This corresponds to an effect size of 0.38 between treatments. We wish to see a difference of this effect size in the QIDS-SR score sustained over the duration of the trial and so will estimate the effect as an area under the curve.
*Power*: All power calculations are for two-tailed tests and alpha = 0.05.

With a sample size of 276 at baseline and 10% loss to follow up, we expect 248.4 patients to complete the trial. The Stata stpower command gave 90% power using a logrank test to detect a difference in the time to discontinuation with 50% (lithium) and 70% (quetiapine) as the proportions of participants remaining on assigned treatment. This determined the lower limit of the sample size. Applying this sample size to the self-report QIDS-SR data we also needed to account for the likely haphazard nature of missing data points at each assessment time point. We used simulation and the non-central chi-square method. Using 1000 samples, a simple random intercept model covarying for baseline, a time dummy variable and with a single average combined treatment effect, this number of participants will provide 99.7% power to detect an effect size of 0.38 (with 1 degree of freedom, χ^2^ = 3.84, and non-centrality parameter = 20.86).

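### The multiplicity adjustment takes in side effects, weight and blood pressure with the efficacy outcomes, which can only lower the chance of detecting a true harm difference

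*Protocol article*

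**What the plan says.** The Secondary outcomes section lists eleven items. Three of the measures in that list describe tolerability: the item "Physical health parameters: weight (kg) and blood pressure (mmHg"), which holds two of them, and the total score on the Patient Rated Inventory of Side Effects (PRISE). The others, apart from SAEs, cover clinician-rated depression, response and remission, global improvement, quality of life, social functioning, adherence, and two time-to-event outcomes.

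The timing rule is: "The secondary outcomes will be measured at 8 and 52 weeks, and differences between lithium and quetiapine assessed at both time points". The scope of the adjustment is: "Secondary outcomes, except for SAEs, will be adjusted for multiple comparisons". The next sentence deals with the one exempt item: "SAEs will be tabulated as number of SAEs in each group, and number of people reporting an SAE in each group over 12 months".

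The section on statistical methods returns to the subject once: "Adjustment for multiple testing will be presented". It gives the method only by citation and makes no exception for any outcome. Nothing elsewhere in the article takes PRISE, weight or blood pressure out of the adjusted set.

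**The concern.** Adjustment for multiple testing limits false positive claims and pays for this with missed true differences. For efficacy claims that is usually a fair exchange. For harms the usual convention is the reverse, because overlooking a real harm is taken to be the costlier error. Under the rule as written, the evidence needed to declare a difference in weight or side effects depends on how many efficacy and functioning scales happen to be in the same list.

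The stake is practical. The trial hopes to say which of two active add-on drugs should be preferred. A difference in weight or side effects that is labelled non-significant after adjustment could be read as equal tolerability.

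The article can reasonably leave the adjustment method to the analysis plan. The scope of the adjustment is a different matter, because the article itself decides it.

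**Working it through.** **The plan's own figure first.** The article gives no power for any secondary outcome. Its stated 90% for time to discontinuation serves as a check on inputs. With 50% and 70% remaining on treatment, the hazard ratio is ln(0.7)/ln(0.5) = 0.515. With 248.4 evaluable patients and an average event proportion of (0.5 + 0.3)/2 = 0.40, expected events are 99.4. Schoenfeld's formula gives 91.2% and Freedman's 89.2%, so the stated 90% reproduces.

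**Inputs for the harm comparisons**
- Two-sided alpha of 0.05, from the Power calculation section: "All power calculations are for two-tailed tests and alpha = 0.05". It is assumed to apply to the secondary outcomes too.
- Number of tests m, which the article does not state. Eleven listed items less SAEs leaves 10. Counting response, remission, weight, systolic and diastolic pressure separately gives 13. Testing the 11 of these that are not time-to-event at both weeks 8 and 52 gives 2 × 11 + 2 = 24. Doubling all 13 gives an outer bound of 26.
- Baseline power of 80% at 0.05, assumed for illustration.

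**Bonferroni.** The shift that gives 80% power is 1.960 + 0.842 = 2.802 standard errors. Power after adjustment is Φ(2.802 − z), where z is the normal quantile at 1 − 0.05/(2m).

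| m | threshold | z | power |
|---|---|---|---|
| 1 | 0.0500 | 1.960 | 80% |
| 10 | 0.0050 | 2.807 | 50% |
| 13 | 0.0038 | 2.890 | 46% |
| 20 | 0.0025 | 3.023 | 41% |
| 26 | 0.0019 | 3.102 | 38% |

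**Less costly methods.** These were simulated with independent tests and 40,000 replicates. Either three tests, or half of all tests, carried a true effect of the same 2.802 standard errors.

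| m | Holm | Benjamini-Hochberg |
|---|---|---|
| 10 | 51–53% | 60–67% |
| 13 | 48–49% | 56–66% |
| 20 | 42–44% | 50–67% |
| 26 | 39–41% | 46–66% |

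The higher figure in each range belongs to the scenario where half of the tests carry a true effect.

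**A second illustration on the trial's scale.** Take a harm difference of 0.38 SD, a figure borrowed from the efficacy calculation, with 124 per arm. The shift is 0.38 × √(124/2) = 2.992. Power is Φ(2.992 − 1.960) = 84.9% unadjusted. Under Bonferroni it is 57.3% (m = 10), 54.0% (m = 13) and 46.6% (m = 24). The chance of a non-significant result rises from 15% to 43%, 46% and 53%.

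**The case against.** There is a serious case that this is a matter of preference. The trial compares two active drugs with two-sided tests, so less weight gain on one of them is itself a comparative claim, and a false difference could mislead prescribing too. Adjusting prespecified comparative secondary outcomes is not a technical error, and no sentence in the article contradicts the choice. This stands as far as it goes: the point is an improvement to the plan, not the correction of a mistake.

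Reporting may also soften the effect. The statement that adjustment will be presented could mean adjusted results shown beside unadjusted ones, and the article does not say that adjusted p-values will decide the conclusions. Adjusting p-values leaves the effect estimates unchanged. These are fair limits on the consequence. Still, the Secondary outcomes section says without qualification that the outcomes will be adjusted. If both sets of results are intended, the text should say so.

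A reader might infer from the SAE exemption that the plan accepts a principle of leaving harms unadjusted and then breaks it. The documents do not support this. Only tabulation is described for SAEs, and an outcome that is merely tabulated has no p-value to adjust. That explains the exemption in full.

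A reader might also cite the Discussion's remark about effectiveness and tolerability to argue that the trial's main tolerability evidence is weakened. That remark describes the primary outcomes, which this rule does not touch.

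**Conclusion.** The point holds in a limited form. The article places PRISE, weight and blood pressure in the same adjusted set as the efficacy, functioning and adherence outcomes. Whatever standard method is used, this can only reduce the chance of declaring a true difference in harm.

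The direction is certain, but the size is not. For a comparison with 80% unadjusted power, the illustrative range is about 38–50% under Bonferroni and 46–67% under Benjamini-Hochberg. These figures rest on an assumed family of 10 to 26 tests, an assumed baseline power and, for the simulated methods, independent tests. Neither the method nor the family can be read from the article.

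It would go too far to conclude that the trial will miss harms, or that its tolerability comparison fails. Time to all-cause discontinuation is a primary outcome outside this rule, and the estimates and intervals for the secondary harm measures remain available to the reader.

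**What to change.** Amend the sentence on scope along these lines: adjustment for multiple comparisons applies to the secondary outcomes other than harms; PRISE total, weight and blood pressure are reported with estimates, 95% confidence intervals and p-values, all labelled as unadjusted; SAEs are tabulated only. Adjusted p-values for the three harm measures may be shown beside the unadjusted ones. No SAE p-values should be added. The sentence on adjustment in the statistical methods section should be aligned with this.

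The change is to wording only and needs no new data, no larger sample and no change to the primary analyses. The downside is a somewhat higher chance of a false harm signal, which the labelling makes visible.

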### Additional outcomes

For a full list of tertiary and ancillary trial outcomes please visit clinicaltrials.gov. Two key ancillary outcomes are detailed below:
**Cost-effectiveness**: This data will be gathered from the Client Service Receipt Inventory (CSRI) [42], modified for TRD, asked at baseline, 8, 26, and 52 week study visits. Cost-effectiveness analyses will be conducted from a health and social care, and a societal perspective. This will include trial and concomitant medication costs, healthcare costs (including hospital, community-based, social and primary care services), costs to statutory and non-statutory services, impact on caregivers and families, and days off work due to health problems.
**Predictors of treatment response**: for example, baseline staging of treatment resistance (Maudsley Staging Method, MSM [32]), depression characteristics (e.g. severity (HDRS [31]), chronicity, family history, recurrence (MINI 7.0), psychiatric comorbidity (MINI 7.0), subtype (e.g. typical versus atypical, clinician rated Inventory of Depressive Symptomatology (IDS-C) [43]), personality (Standard Assessment of Personality [44]), type of antidepressant (e.g. selective serotonin reuptake inhibitor (SSRI) vs. non-SSRI), hypomanic symptoms (16-item hypomanic checklist (HCL-16) [45] at baseline) and sociodemographic factors (e.g. sex, age, ethnicity, body mass index). Briefly, the analysis would build a predictive model of response using an appropriate variable selection procedure (i.e. manual forward stepwise regression).

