### Objectives and hypothesis

This study aims to determine whether the decision to prescribe quetiapine is more clinically and cost effective than the decision to prescribe lithium over a longer term in a randomised clinical trial powered to detect superiority. We propose a 12 month follow up period, hypothesising that quetiapine will be superior to lithium in terms of our primary outcomes: time to all-cause treatment discontinuation and average depressive symptom burden over 12 months.

We hope to help shape a modified treatment pathway for TRD in which one augmenter is preferential to the other. However, if quetiapine is not found to be clinically superior based on our primary and secondary outcomes, the results of the cost effectiveness analysis, or individual level predictive factors, may determine the most appropriate choice for each patient.

The trial will recruit patients with TRD: defined as the failure to adequately respond to two or more therapeutic trials of antidepressant treatments in the current episode (at adequate dose and duration) [3, 8]. This definition of treatment resistance is in line with the point at which treatment augmentation is recommended in clinical practice [3] and at which the evidence suggests clinical equipoise between the two treatments [20].

This protocol paper is consistent with SPIRIT (Standard Protocol Items: Recommendations for Interventional Trials) 2013 recommendations [28] (checklist attached).

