## Discussion

This protocol paper describes a pragmatic randomised clinical trial designed to determine whether the decision to prescribe quetiapine is more clinically and cost effective than lithium for patients with TRD over 12 months. The chronicity of TRD, in which patients often fluctuate between states of remission and relapse [51], highlights not only the importance of this research question, but also the implementation of a 12 month follow up period. As discussed, there have been no direct head-to-head comparisons of these treatments with a follow up period of greater than six weeks. This is insufficient given that up to 80% of patients with TRD relapse within 12 months of responding to treatment [8, 20]. Our choice of primary outcome, a longitudinal measure of depression severity (QIDS-SR), measured weekly over 12 months via the True Colours system (www.truecolours.nhs.uk), recognises the highly fluctuating nature of this disorder. True Colours has been used to assess mood in prior research studies with success [52] and facilitates the monitoring of all cause treatment discontinuation across the full duration of the trial.

The benefits of determining whether one of these recommended and widely prescribed medications is more effective for patients with TRD are clear. However the results of this study should also positively impact secondary care mental health teams and the wider NHS by helping to minimise relapse rates and in doing so alleviate some of the financial and time burden placed on mental health services. If there is no significant difference between lithium and quetiapine in the primary outcomes of clinical effectiveness, the cost-effectiveness analysis, which takes into account the different monitoring requirements for these medications, may benefit health bodies by informing them of the most cost-effective of these two treatment options. In addition, our further analyses may contribute to the growing body of research examining predictors of treatment response in depression, and the development of personalised mental health care.

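### The predictor analysis is a manual forward stepwise model of response, which as described finds prognostic factors and not which drug suits which patient, although the protocol hopes to guide that choice from predictive factors

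*Protocol article*

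**What the plan says.** Under Additional outcomes, the protocol article introduces the predictor analysis with the words "Two key ancillary outcomes are detailed below", so it is ancillary but singled out. The analysis is to "build a predictive model of response using an appropriate variable selection procedure (i.e. manual forward stepwise regression"). The abbreviation before the method is i.e. and not e.g., so the procedure is named and not offered as one option among several.

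The candidates are introduced as examples. They start with "baseline staging of treatment resistance (Maudsley Staging Method, MSM [32]), depression characteristics (e.g. severity (HDRS [31]), chronicity, family history, recurrence (MINI 7.0), psychiatric comorbidity (MINI" and run on to "sociodemographic factors (e.g. sex, age, ethnicity, body mass index". Counting each named characteristic once gives 14.

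Under Objectives and hypothesis, the article considers the case where quetiapine is not found clinically superior. Two things may then settle the matter: the cost-effectiveness results, or "individual level predictive factors, may determine the most appropriate choice for each patient". The Discussion is softer: "our further analyses may contribute to the growing body of research examining predictors of treatment response in depression".

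The short description gives no entry threshold, shrinkage, internal validation or treatment-by-predictor term. Under Secondary outcomes, adjustment for multiple comparisons is stated for those outcomes only. A full statistical analysis plan is promised under the statistical methods heading and is not at hand.

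**The concern.** There are two problems, and the first matters more.

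- **Purpose and model differ.** To choose between lithium and quetiapine for a given patient, one must know whether a characteristic changes the difference between the drugs. That is effect modification, estimated by a treatment-by-predictor interaction. A model of response across the trial estimates prognosis: who improves, whichever drug is given. A strong prognostic factor can leave the choice of drug untouched, and a factor that reverses the preferred drug can have no average association with response.
- **The selection method is optimistic.** Forward stepwise selection keeps the candidates that happen to look strongest, then reports their coefficients and fit as if they had been chosen in advance. With a long, open list and about 248 patients, some retained predictors may be chance findings, and effects and discrimination will look better than they are. Steps taken by hand are also hard to repeat in resamples unless they follow a written rule.

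What is at stake is the reading of a neutral trial. The objectives name predictive factors as one of two ways to guide choice in that case. Prognostic or chance findings could then be taken as advice on which drug to prescribe.

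**Working it through.** **Inputs from the protocol article**
- Named candidates (Additional outcomes): staging of resistance, severity, chronicity, family history, recurrence, psychiatric comorbidity, subtype and personality (8), plus antidepressant type, hypomanic symptoms, sex, age, ethnicity and body mass index (6). Total 8 + 6 = 14.
- Patients (Power calculation): "With a sample size of 276 at baseline and 10% loss to follow up, we expect 248.4 patients to complete the trial". I use 248.
- Significance level (Power calculation): "All power calculations are for two-tailed tests and alpha = 0.05". This covers the power calculations only.

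**Assumptions**
- Entry threshold 0.05, with 0.01 to 0.157 shown, because none is stated.
- 40% response in the null simulations.
- The effect sizes in step 3.

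**1. The plan's own figure.** The predictor analysis has no stated error rate or power to reproduce. The trial's 90% logrank power, which fixes the sample size used here, does reproduce. HR = ln 0.7 / ln 0.5 = 0.515; events = 248 × 0.40 = 99.2. Schoenfeld: Φ(0.664 × √99.2 / 2 − 1.96) = Φ(1.35) = 91%. Freedman: Φ(√99.2 × 0.485 / 1.515 − 1.96) = Φ(1.23) = 89%.

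**2. False selection when no candidate predicts anything.** For k independent null candidates and entry at α, P(at least one enters) = 1 − (1 − α)^k.

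| k | α | P(at least one) |
|---|---|---|
| 14 | 0.01 | 13% |
| 14 | 0.05 | 1 − 0.95^14 = 51% |
| 14 | 0.10 | 77% |
| 14 | 0.157 | 91% |
| 8 | 0.05 | 34% |
| 25 | 0.05 | 72% |

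At k = 14 and α = 0.05, the expected number of false entries is 14 × 0.05 = 0.70. Simulated forward selection (binary response, linear approximation, n = 248 and 276) gave about 52% with independent candidates and 44–46% with pairwise correlation 0.3. When anything was selected with independent candidates at n = 248, the mean apparent c-statistic was 0.60 against a true 0.50.

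**3. Prognostic factor against moderator.** The setting is one standardised predictor, a continuous outcome with residual SD 1, 124 patients per arm and tests at 0.05. Both models include treatment.
- Purely prognostic factor, 0.3 SD per SD, same in both arms. Main effect: SE = 1/√248 = 0.0635, z = 4.72, power Φ(4.72 − 1.96) = 99.7%; simulated 99.7%. The interaction test flags it in 5.4%, its nominal error rate.
- Pure moderator, slopes +0.2 and −0.2 by arm. The main effect is zero and was picked up in 6.0% of simulated trials. Interaction: difference in slopes 0.4, SE = √(1/124 + 1/124) = 0.127, z = 3.15, power Φ(3.15 − 1.96) = 88%; simulated 87%.

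A main-effects model therefore nearly always finds the factor that does not bear on choice of drug, and finds the one that does at about the false-positive rate.

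**4. Power for interactions.** The 0.4 difference in slopes is large. At 0.2, z = 1.57 and power is Φ(1.57 − 1.96) = 35%. With a Bonferroni threshold of 0.05/14 = 0.0036 (critical z 2.91), power for the 0.4 difference falls to Φ(3.15 − 2.91) = 59%.

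**The case against.** The best defence is that this is one short sentence about an ancillary outcome, and that a full analysis plan is promised. Thresholds, interaction terms, arm-specific models and validation are the kind of detail such a plan supplies. A reader might infer that the analysis cannot show which drug suits which patient. The article does not support that: it neither includes nor excludes treatment-by-predictor terms, and forward selection can contain them. The 6% against 87% contrast assumes a main-effects model. This part of the defence stands, so the point is limited to the model as described. It does not remove the point, because the selection procedure itself is named, and so is the outcome modelled: response, not difference in response.

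A reader might also infer that the plan will find spurious predictors about half the time. That is not a figure from the article. It needs entry at 0.05, exactly 14 roughly independent candidates and no true predictor. The last is doubtful, since severity and number of failed treatments were thought important enough to stratify on. Nor is it peculiar to stepwise selection: fitting all 14 null candidates in one model with no selection gave at least one p<0.05 in 49% of simulated trials. The objection to stepwise selection rests on optimism in effects and fit, not on this figure.

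Two further limits stand. Manual selection can be validated by resampling if its steps follow a fixed rule that can be scripted. And elastic net is no cure by itself: in the same null setting, tuned to minimum cross-validation error, it kept at least one noise variable in 35% of runs, against about 3–4% with the one-standard-error rule. A tuning rule has to be stated.

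Finally, the objectives say only that predictive factors may determine choice, and do not tie this expressly to the stepwise model.

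**Conclusion.** The point holds in limited form, as an optional improvement. The article names a selection method prone to optimism and describes a model of response, while its objectives look to predictive factors to guide choice between the drugs. As described, the model does not answer that question. The mismatch depends on no entry threshold; its illustrated size (99.7% and 6% for the main-effects model, about 87% for the interaction test) rests on the assumed slopes, a continuous outcome and main effects only. The false-selection figure is conditional: 51% at 0.05 with 14 independent null candidates, 13% to 91% over thresholds from 0.01 to 0.157. The unseen analysis plan may already contain interaction terms and validation. The analysis is ancillary, so no primary or secondary conclusion changes.

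**What to change.** In the statistical analysis plan, replace manual forward stepwise selection with the following:
- a closed, pre-listed set of candidate moderators;
- a model containing treatment, the predictors and treatment-by-predictor terms;
- either penalised regression with a prespecified tuning rule (for example one-standard-error), or the full prespecified model with multiplicity-adjusted interaction tests;
- a script for the whole procedure, repeated in each bootstrap sample, with optimism-corrected performance reported;
- statements about choice of drug drawn from the interaction terms only and labelled exploratory. Prognostic findings can be reported separately as such.

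The cost is plan wording and modest extra analysis. Fewer predictors will be reported, and power for interactions is limited, as step 4 of the working shows, so a null result should not be read as absence of moderation.
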